### Participant Timeline and Study Schedule

This health care provider–level crossover pilot is planned over a 12-month period. Months 0 to 2 will be used for finalizing the platform and completing quality assurance of the simulated case library. The first study period will then be conducted during months 2 to 4, followed by a 1-week washout period to reduce potential carryover effects. The second study period will take place during months 4 to 6. After completion of both periods, participants will complete postperiod surveys assessing usability, trust, and cognitive workload, followed by brief semistructured debrief interviews. The remaining months will be dedicated to data cleaning, analysis, qualitative review, and final reporting.

### Sample Size

At least 36 health care providers (32 cases/health care provider) yield 1150 to 1280 paired decisions. Under pilot assumptions (accuracy 0.60 usual care vs 0.75 FibroX), McNemar test provides >80% power to detect a 15-point improvement at α=.05 after accounting for health care provider–level clustering via a conservative design effect. Precision estimates for feasibility and usability metrics are expected to be narrow enough to inform a subsequent multicenter trial.

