## Methods

### Trial Design and Oversight

We will conduct a 12-month, health care provider–level, randomized, 2‑period crossover simulation trial to evaluate the feasibility, usability, and preliminary effectiveness of FibroX, an explainable AI decision support tool for detecting MASLD‑associated advanced liver fibrosis (≥F3) in adults with T2D. Because FibroX is not currently used in routine clinical care, this study evaluates the tool in a simulated clinical environment. Each clinician serves as their own control (FibroX-enabled care vs usual care), separated by a 1-week washout. Distinct, nonoverlapping simulation case sets will be used in each study period, such that clinicians will not evaluate the same cases across periods, reducing case-recall bias and minimizing carryover related to prior exposure. The study involves no patient enrollment and uses deidentified or synthetic cases. Oversight is by the principal investigator and study steering team; a formal Data Monitoring Committee is not required given the minimal risk.

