### Outcomes

The primary end points of this pilot study are the feasibility and usability of FibroX-enabled care within diabetes-focused clinical workflows. Feasibility will be assessed using recruitment and study completion rates, with prespecified targets of enrolling at least 70% of eligible clinicians and achieving a completion rate of at least 85% among enrolled participants. Completion will be defined as participants completing both simulation periods, including all assigned cases and postperiod surveys. Participants who do not complete both periods or required assessments will be classified as incomplete. Usability will be evaluated using the System Usability Scale (SUS), with a prespecified success threshold of 70 or higher.

Secondary end points include workflow efficiency and preliminary diagnostic performance. Workflow efficiency will be assessed by median time per case, with an anticipated threshold of 3.5 minutes or less. Preliminary diagnostic performance outcomes will include sensitivity, specificity, and the area under the receiver operating characteristic curve for the detection of MASLD-associated advanced fibrosis. Calibration will be examined using intercept, slope, and graphical assessment of predicted versus observed risk.

Exploratory end points will include clinician trust and cognitive workload, assessed using the AI trust scale and National Aeronautics and Space Administration Task Load Index (NASA-TLX), respectively, as well as implementation-related outcomes, including the proportion of guideline-concordant referrals and net reclassification improvement. Qualitative debrief interviews will further explore clinician understanding, interpretability, and perceived usefulness of the SHAP-based explanations, including how these outputs influence decision-making and trust in the model. These measures are intended to provide pilot estimates and inform the design, end point selection, and sample size considerations for a future definitive trial.

At a high level, this pilot will be considered successful if predefined feasibility and usability thresholds are met, including adequate recruitment and completion rates and a SUS score of 70 or higher, alongside signals of acceptable workflow efficiency and improved or comparable diagnostic performance relative to usual care. These criteria are intended to determine whether progression to a larger, real-world trial is justified.

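### The 1150 to 1280 paired decisions are clinicians × cases, not pairs, and the stated >80% power, given for overall accuracy, cannot be checked and does not cover the sensitivity and specificity tests

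*Protocol article*

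**What the plan says.** The Sample Size section sets the size as "At least 36 health care providers (32 cases/health care provider"), and says that these "yield 1150 to 1280 paired decisions". It does not say whether 32 is each clinician's total or the number per period. The assumed rates are "accuracy 0.60 usual care vs 0.75 FibroX", and the claim is that "McNemar test provides >80% power to detect a 15-point improvement at α=.05", "after accounting for health care provider–level clustering via a conservative design effect". No design effect, intraclass correlation (ICC) or discordance rate is given.

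Four other places bear on this:
- Trial Design and Oversight: "Distinct, nonoverlapping simulation case sets will be used in each study period". The same sentence adds that a clinician does not see a case in both periods.
- Statistical Analysis: McNemar tests are applied to sensitivity and to specificity. A mixed-effects logistic model with a clinician random effect is also planned, and all clinician decisions are analysed.
- Outcomes: diagnostic performance is secondary. The feasibility target includes "achieving a completion rate of at least 85% among enrolled participants".
- Participants: the case library is to be balanced across fibrosis stages, but the share with stage F3 or higher is not given.

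**The concern.** McNemar's test needs matched binary observations. The natural match here would be one clinician judging one case under both conditions, and the design rules that out. A count of more than a thousand pairs therefore describes a different trial from the one in the design section.

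The power is also stated for overall accuracy, while the named McNemar tests are on sensitivity and specificity. Each of those uses only the cases with, or only the cases without, advanced fibrosis.

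This is the only power calculation in the article, and improved or comparable diagnostic performance is part of the pilot's success criteria. A reader could take a non-significant sensitivity comparison as adequately powered when nothing in the document shows that it is.

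**Working it through.** **1. Reproduce the count.** Inputs from Sample Size: 36 clinicians and 32 cases each. 36 × 32 = 1152. The upper end matches 40 × 32 = 1280. The range is clinicians × cases, with every clinician contributing every case.

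**2. Count the pairs.** With non-overlapping case sets, same-clinician same-case pairs number zero, whatever 32 means.

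| Reading of 32 | Decisions per condition, 36–40 clinicians | 31 clinicians |
|---|---|---|
| Total over both periods (equal split assumed, 16 each) | 576–640 | 31 × 16 = 496 |
| Per period | 1152–1280 | 31 × 32 = 992 |

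The figure of 31 comes from the 85% completion target: 0.85 × 36 = 30.6.

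**3. Check the power for overall accuracy.** Take the McNemar formula at face value, with d = 0.15 and two-sided α = .05. Discordance ψ is not stated. If the two responses are independent, ψ = 0.60 × 0.25 + 0.40 × 0.75 = 0.45.

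Effective pairs for 80% power = [1.96√ψ + 0.84√(ψ − d²)]² / d². At ψ = 0.45 this is [1.96√0.45 + 0.84√0.4275]² / 0.0225 ≈ 154.6.

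Largest design effect that keeps 80% power:
- 1152 / 154.6 ≈ 7.5
- 576 / 154.6 ≈ 3.7
- 496 / 154.6 ≈ 3.2

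At the largest possible discordance, ψ = 0.65, about 225 effective pairs are needed, and the limits for 576 and 496 fall to about 2.6 and 2.2. An unpaired comparison needs 152 per condition, close to the value at ψ = 0.45. The claim for overall accuracy therefore holds over a wide range, even after halving the count and losing 15% of clinicians. Whether it holds for the protocol's own design effect cannot be checked, because that value is not given.

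**4. Move to sensitivity.** Assume that 40% of cases are F3 or higher (two of five equally represented stages, F0–F4) and that there are 31 clinicians.
- 16 cases per condition: 31 × 16 × 0.40 ≈ 198 decisions; 198 / 154.6 ≈ 1.28.
- 32 cases per condition: 31 × 32 × 0.40 ≈ 397 decisions; 397 / 154.6 ≈ 2.57.

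The room for clustering is much smaller than for overall accuracy, above all on the 16-case reading.

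**5. Allow for the crossover.** A design effect of the form 1 + (m − 1) × ICC treats a clinician's results under the two conditions as unrelated. In a crossover a stable clinician effect largely cancels. Simulated power for sensitivity of 0.60 versus 0.75, with 31 clinicians, 6–7 positive cases per condition and a clinician-level paired t test, is:

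| Clinician ability across conditions | ICC 0.05 | ICC 0.10 | ICC 0.20 |
|---|---|---|---|
| Fully shared | about 89% | about 90% | about 93% |
| Uncorrelated | about 80% | about 70% | about 60% |

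Repeat simulations differed by a point or two, reaching up to 95% with shared ability. The range is thus about 60% to 95%.

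**The case against.** The strongest reply is that the power statement concerns overall accuracy only and has not been shown to be false. That stands. A reader might infer from the faulty pair count that power above 80% is wrong, but step 3 shows that it survives halving and attrition unless clustering is heavy. The statement is unverifiable and mismatched to the named tests, not refuted.

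A reader might also infer that sensitivity loses 80% power once the clinician ICC exceeds about 0.05. That follows only if a clinician's ability is uncorrelated between conditions. With shared ability, power stays near 90% or above. Lower figures can be produced by adding random variation between cases, but they depend on assumed adherence to FibroX and an assumed FibroX accuracy, neither of which the document gives, so they are not relied on here.

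Calling the range total decisions goes too far as well. That is right only if 32 spans both periods; if 32 is per period, 1152 is the number per condition.

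On dropout, the lower end of the range equals 36 clinicians with full data. But 36 is a minimum, 85% is a feasibility target and not a planning assumption, and a clinician who misses only a survey counts as incomplete with all decisions recorded. Since all decisions are analysed, 31 clinicians is a worst case.

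Finally, the analysis section also names a primary comparison of diagnostic accuracy and a mixed model, so overall accuracy may well be analysed. None of this rescues the pair count.

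**Conclusion.** The count is wrong as labelled: 1150 to 1280 is clinicians × cases, and the design yields no same-clinician same-case pairs under either reading of 32. This part needs no assumption. McNemar power computed on those pairs therefore has no basis in the design.

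The power figure above 80% for overall accuracy is neither confirmed nor disproved. It gives no assurance for sensitivity or specificity. For sensitivity, power for a 15-point gain is about 60% to 95%, assuming 40% F3 or higher, 16 cases per condition, 31 clinicians and an ICC of 0.05 to 0.20. It depends mainly on how far a clinician's ability carries over between conditions. With 32 cases per condition, about twice as many decisions bear on sensitivity and the position is better.

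This should be fixed, but it does not threaten the trial: the primary endpoints are feasibility and usability and do not rest on this figure.

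**What to change.** Rewrite the Sample Size paragraph to:
- state cases per clinician per period, and decisions per condition, for 36 clinicians (576 or 1152) and after 15% non-completion (496 or 992), with the latter marked as a worst case because all decisions are analysed;
- delete the word paired and the McNemar power;
- base any power statement on the clustered crossover model, with the ICC and the within-clinician correlation between conditions stated;
- state the planned share of cases with F3 or higher, and give expected confidence-interval half-widths for sensitivity and specificity, or say plainly that the pilot is not powered for those comparisons.

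The McNemar tests named in Statistical Analysis meet the same pairing problem and should be reconciled with the mixed model at the same time.

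The cost is a recalculation and one rewritten paragraph, with a stated figure that may look less favourable. No extra participants are needed, and the article reports that recruitment had not begun.

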### Randomization, Allocation Concealment, and Implementation

Health care providers will be randomized 1:1 to AB (FibroX then usual care) or BA (usual care then FibroX) using a computer-generated schedule prepared by a statistician not involved in recruitment (Figure 2). Allocation will be concealed via a secure, centralized randomization module until assignment. The research coordinator enrolls participants and implements sequence assignments.

**Figure 2 figure2:**
[figure not shown]
FibroX health care provider–level crossover randomized controlled trial pilot design. DO: doctor of osteopathic medicine; EHR: electronic health record; FTE: full-time equivalent; MD: doctor of medicine; NP: nurse practitioner; PA: physician assistant; T2D: type 2 diabetes.

### Blinding

Blinding of health care providers is not feasible due to visible tool features. Outcome assessors and data analysts are masked to sequence assignment; datasets use anonymized identifiers.

### Data Collection Methods

The platform automatically logs case navigation, decisions, timestamps, and use of FibroX features and overrides. Clinicians will not receive case-level performance feedback during either simulation period. Feedback, if provided, will be deferred until completion of the study period to minimize within-period learning effects. Surveys (SUS, AI trust, and NASA‑TLX) are administered electronically at the end of each period. Qualitative debriefs are audio-recorded and transcribed for thematic analysis. Completeness checks and range validations occur at ingestion.

### Statistical Analysis

All analyses will follow an intention-to-treat principle, including all health care provider decisions regardless of sequence assignment. The primary comparison of diagnostic accuracy between FibroX-enabled care and usual care will use paired analyses to account for the crossover design. Sensitivity and specificity for detecting MASLD-associated advanced fibrosis will be compared using McNemar test for paired proportions. Overall discrimination will be assessed by calculating the area under the receiver operating characteristic curve for each condition, and calibration will be evaluated through intercept, slope, and calibration plots to determine agreement between predicted probabilities and observed outcomes.

To account for clustering at the health care provider level and the crossover design, mixed-effects logistic regression models will be used, specifying health care provider as a random effect and study condition, study period, and sequence assignment as fixed effects. Sensitivity analyses will also assess whether diagnostic performance differs by sequence assignment or period, which may suggest residual carryover or learning effects. These models will also adjust for case-level covariates such as age, BMI, and HbA_1c_ to explore potential confounding and heterogeneity. Secondary analyses will include net reclassification improvement to quantify whether FibroX improves assignment of cases into clinically appropriate triage categories compared with usual care. Bootstrap resampling will be used to generate CIs for net reclassification improvement and calibration metrics, ensuring robust estimation under small-sample conditions.

Feasibility outcomes, including recruitment and completion rates, will be summarized descriptively with proportions and 95% CIs. Usability and trust scores from the SUS and AI trust scale will be analyzed using paired *t* tests or Wilcoxon signed-rank tests, depending on distributional assumptions. Cognitive workload scores from NASA-TLX will be compared similarly. Subgroup analyses will explore whether diagnostic performance varies across diabetes-related characteristics such as HbA_1c_, BMI, and duration of diabetes, using interaction terms in mixed-effects models. Missing data are expected to be minimal; if more than 5% of survey data are missing, multiple imputation under a missing-at-random assumption will be applied, with sensitivity analyses conducted using complete-case data. All statistical tests will be 2-sided with an α level of .05, and analyses will be performed using the R (R Foundation for Statistical Computing) or Python (Python Software Foundation) statistical packages.

To aid interpretation of the crossover design, sequence, period, and potential carryover effects will be explicitly examined. Sequence effects (AB vs BA) will assess whether the order of exposure to FibroX influences outcomes. Period effects will evaluate whether outcomes differ between the first and second study periods, independent of the intervention, which may reflect learning or temporal effects. Potential carryover effects will be explored by assessing interaction terms between intervention and study period and by comparing outcomes across sequences; a significant difference by sequence or interaction with period would suggest residual carryover. If meaningful carryover effects are detected, sensitivity analyses restricted to first-period data will be performed.

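### The McNemar test and the count of paired decisions assume clinician-case pairs that the non-overlapping case sets rule out

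*Protocol article*

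**What the plan says.** Three sections of the protocol article bear on this.

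- **Trial Design and Oversight:** "Distinct, nonoverlapping simulation case sets will be used in each study period, such that clinicians will not evaluate the same cases across periods". The stated purpose is to limit case recall and carryover. Randomization and Table 1 give each clinician one condition per period, in order AB or BA.
- **Statistical Analysis:** the main accuracy comparison "will use paired analyses to account for the crossover design", and sensitivity and specificity for "advanced fibrosis will be compared using McNemar test for paired proportions". The next paragraph plans a mixed-effects logistic model with a random clinician effect and fixed effects for condition, period and sequence. It also plans "net reclassification improvement to quantify whether FibroX improves assignment of cases into clinically appropriate triage categories compared with usual care", with bootstrap intervals.
- **Sample Size:** "At least 36 health care providers (32 cases/health care provider) yield 1150 to 1280 paired decisions". Power above 80% is then claimed for McNemar at accuracy 0.60 against 0.75, two-sided 0.05, after a design effect whose value is not given.

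The Interventions section says that usual care presents the same standardized case information. In context this describes what the interface shows. It does not say that a clinician meets the same case twice.

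**The concern.** McNemar's test uses discordant pairs: one unit observed under both conditions, right under one and wrong under the other. The crossover pairs clinicians. It does not pair decisions, because the cases differ between a clinician's two periods. To fill a McNemar table, the analyst would have to match unrelated cases, and no matching rule is given. For sensitivity the matching would have to be made among cases with advanced fibrosis, and nothing says that the two case sets hold equal numbers of them.

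Three things are at stake. The test named for sensitivity and specificity has no proper input. If it is run on made-up pairs, its error rate is not controlled. The only power statement in the article rests on the same pairs. Diagnostic performance is a secondary outcome, but Outcomes includes improved or comparable performance against usual care among the criteria for calling the pilot a success and moving to a larger trial.

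**Working it through.** **1. Count of pairs.** From Sample Size: 36 clinicians, 32 cases each. 36 × 32 = 1152, which matches the lower figure. The upper figure implies 1280 / 32 = 40 clinicians. So the stated range is clinicians × cases. The article does not say whether 32 is per period or in total.

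| Reading of 32 | Decisions per condition (36 clinicians) | Clinician-case pairs |
|---|---|---|
| Total per clinician (16 per period) | 36 × 16 = 576 | 0 |
| Per period | 36 × 32 = 1152 | 0 |

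**2. The stated power.** It cannot be reproduced as a single figure, because neither the discordance ψ nor the design effect is given. The number of pairs needed for 80% power is [1.96√ψ + 0.842√(ψ − d²)]² / d², with d = 0.75 − 0.60 = 0.15. If the two decisions are independent, ψ = 0.75 × 0.40 + 0.25 × 0.60 = 0.45. Then n = (1.315 + 0.550)² / 0.0225 ≈ 155 pairs. Over the possible range of ψ, from 0.15 to 0.65, n runs from 50 to 225. With 1152 true pairs and ψ = 0.45, 80% power would hold up to a design effect of 7.45. The claim is attainable on its own terms, but the pairs do not exist.

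**3. Power without pairs.** For two independent proportions with mean 0.675, n per condition = [1.96√(2 × 0.675 × 0.325) + 0.842√(0.60 × 0.40 + 0.75 × 0.25)]² / 0.15² = (1.298 + 0.550)² / 0.0225 ≈ 152. Design effect = 1 + (m − 1) × ICC, with m decisions per clinician per condition. The ICC values are assumptions, since the article gives none.

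| ICC | Power, m = 16 (576 per condition) | Power, m = 32 (1152 per condition) |
|---|---|---|
| 0.05 | 0.985 | 0.998 |
| 0.10 | 0.933 | 0.969 |
| 0.20 | 0.779 | 0.820 |
| 0.30 | 0.641 | 0.670 |

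The largest design effect that keeps 80% power is 576 / 152 = 3.79, an ICC of 2.79 / 15 ≈ 0.19, or 1152 / 152 = 7.58, an ICC of 6.58 / 31 ≈ 0.21. Applying the full clinician design effect is pessimistic for a within-clinician contrast.

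**4. Type I error of McNemar on made-up pairs.** Simulation with no true effect: 36 clinicians in AB/BA, one case set per period, random matching within clinician, 1500 runs per scenario. Assumed SDs on the logit scale were 0.5 between clinicians and 0.8 between cases. The SD of clinician-by-condition variation was varied. Simulation error near 5% is about √(0.05 × 0.95 / 1500) = 0.6 percentage points.

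| SD, clinician by condition | McNemar, 16 cases per period | McNemar, 32 cases per period |
|---|---|---|
| 0 | 3.1% | 4.2% |
| 0.3 | 6.7% | 9.1% |
| 0.5 | 12.8% | 17.1% |

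A clinician-level crossover comparison, which takes each clinician's difference in proportion correct and averages it over sequences, stayed between 4.5% and 5.7% throughout. The McNemar p-value also depends on the arbitrary matching. In one simulated dataset, re-matching the same decisions moved it between 0.037 and 0.057.

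**5. Net reclassification.** This index needs the same case placed in a triage category under both conditions. No single clinician supplies that. If everyone shares one case set per period, AB clinicians judge that set with FibroX while BA clinicians judge it under usual care. An index across clinicians could then be formed. The article does not describe one.

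**The case against.** The strongest reply is that a valid analysis is already in the plan. The mixed-effects model needs no case pairs and accounts for clinicians. This stands: a reader might infer that the whole plan ignores clustering, but that is true only of the McNemar test. It does not rescue the test, because Statistical Analysis assigns sensitivity and specificity to McNemar by name and gives no precedence if the two analyses disagree.

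A reader might also infer that arbitrary matching can swing the result at will. With 576 decisions per condition and accuracy 0.60 against 0.65, matching correlations of 0, 0.3 and 0.5 give p = 0.080, 0.037 and 0.014. The documents do not support that as a likely outcome. The 5-point gap is not the protocol's, and random matching does not normally produce such correlations. In 20,000 random re-matchings of such data with no clinician effect, the central 95% of p-values ran from 0.075 to 0.101 and none fell below 0.05. At the protocol's 0.60 against 0.75, every re-matching gave p below 0.000001.

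Two further readings go too far. The trial is not shown to be underpowered, by step 3. Nor is net reclassification impossible: only a within-clinician version is, and the full analysis plan may define another.

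Finally, the outcome is secondary and described as preliminary. That limits the damage, but the result still feeds the progression decision.

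**Conclusion.** The contradiction is in the article itself and does not depend on any assumption: the design section removes the clinician-case pairs that Statistical Analysis and Sample Size rely on. The named test is wrong as written and should be corrected before recruitment.

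The size of the harm does rest on assumptions. Under the variance components above, McNemar on made-up pairs is slightly conservative if clinicians respond alike to the tool. It rejects about 7% to 17% of the time under no effect if their responses vary. The inflation comes from treating decisions as independent; the arbitrary matching adds a smaller, avoidable dependence on case order. The claim of more than 80% power can stand up to an ICC of about 0.2, so its basis needs correcting even though the number of clinicians may be adequate.

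**What to change.** **Statistical Analysis.** Delete McNemar. Make the mixed-effects logistic model the accuracy analysis, fitted separately in cases with and without advanced fibrosis (F3 or higher). Keep condition, period and sequence as fixed effects, with clinician and case as crossed random effects. Report marginal risk differences with 95% CIs. A random clinician intercept alone does not capture differing responses to the tool, so let the condition effect vary by clinician where the data allow. Report the period-adjusted clinician-level difference in proportion correct as a check.

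**Sample Size.** Replace paired decisions with decisions per condition. State whether 32 cases is per period or in total. Restate power on an unpaired, clustered basis with the ICC and design effect given.

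**Net reclassification.** Choose one of two routes:
- Define a between-clinician version, comparing AB and BA clinicians on the same case in the same period. This requires that all clinicians share that period's case set. Bootstrap by clinician.
- Report the difference between conditions in the proportion of cases given the correct triage category, separately with and without advanced fibrosis.

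**Cost.** Revised analysis wording and a redone power statement. The correction itself calls for no extra clinicians, cases or data. Whether 36 clinicians suffice depends on the ICC that the sponsor can justify.
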